### 9.3.5.2.2 Clinician Administered Dissociative States Scale (CADSS)

CADSS is a clinician administered rating scale that assesses dissociative symptoms. Twenty-three subjective items, rated 0-4 will be assessed. The assessment takes approximately 5 minutes to administer.

CADSS will be administered by the investigator or a trained designee at specified timepoints indicated in Sections 9.1 and 9.2. Subjects will be rated outside of the MRI scanner for all timepoints. For post-ketamine ratings, subjects will be instructed to answer questions with regards to their experience during the resting BOLD fMRI scan. Results are to be included in the subject's study record.

### 9.3.6 Assessments of Pharmacokinetics (PK)

#### 9.3.6.1 MGS0008

Plasma samples will be analyzed to determine the concentration of MGS0008 using a validated, specific and sensitive liquid chromatography - tandem mass spectrometry (LC-MS/MS) method. A description of the bioanalytical methods will be included in the final report. The determination of MGS0008 will be performed by [REDACTED]

##### 9.3.6.1.1 Blood Sampling (MGS0008)

Blood samples for determination of PK of MGS0008 will be collected at Day 6, 3 hours post administration of investigational product. The date and time of blood sampling and the last investigational product administration before blood sampling must be recorded in the subject's study records.

Blood collection tubes: 10 mL plastic vacuum tubes containing heparin sodium.

Plasma sample storage vessels: 2.0 mL polypropylene cryovials

Labeling: The labels on tubes for plasma samples should include: the protocol number, subject number, study day, nominal time point, sample type (e.g., MGS0008 PK Plasma), aliquot type (Primary or Backup), and barcode / barcode number (if applicable).

After collection, the blood sample will be kept in an ice bath (or other cooling systems, except for refrigerator) until centrifuged. Sample must be centrifuged (4°C, 3000 rpm, 10 min.) within 30 minutes after blood collection to obtain plasma. After centrifugation, plasma sample shall be distributed into two polypropylene tubes, in which 11% acetic acid (50 µL) was added beforehand (volume of acetic acid may be adjusted depending on obtained plasma volume), as follows:

- 0.5 mL (Primary) for MGS0008 pharmacokinetic analysis
- 0.5 mL (Backup) for MGS0008 pharmacokinetic analysis

All tubes shall be stored at or below -70°C.

#### **9.3.6.1.2 Shipping (MGS0008)**

##### Shipment of Samples

Site staff personnel will send frozen samples under dry ice to the measurement institution shown below. The coordinating investigator will retain copies of shipment documents generated at the time of shipping. Shipment to the measurement facility will be carried out in two separate batches (primary and backup). All samples will be transported by World Courier with fax/email confirmation of receipt.

##### Shipping Address

Plasma samples for MGS0008 measurement will be shipped to:

[REDACTED]  
[REDACTED]  
[REDACTED]  
[REDACTED]  
[REDACTED]

#### **9.3.6.2 Ketamine**

Plasma samples will be analyzed to determine concentrations of ketamine. The determination of ketamine will be performed by the Analytical Psychopharmacology Laboratory at the Nathan S. Kline Institute (NKI).

Blood samples (10 mL) for determination of PK of ketamine will be collected on Final Screening Visit and Day 6, at 5 minutes after cessation of the MRI scan. The date and time of blood sampling must be recorded in the subject's study records. Instructions for preparation, storage and shipping of PK (ketamine) samples are found in the laboratory manual.

#### **9.3.7 Pharmacogenomic (PGx) Blood Sampling**

A single blood sample (8.5 mL) for PGx will be collected into a PAXgene™ Blood DNA tube for initial screening eligible subjects during Final Screening Visit. Only subjects who have consented to allow PGx research may have sample collected. The subject may choose to participate in the trial, but not participate in the PGx research. Instructions for preparation, storage and shipping of the PGx samples are found in the laboratory manual. The date of blood

sampling must be recorded in the subject's study records.

### 9.3.8 Blood Sample Volume for the Study

The total blood volume withdrawn from any single subject for all blood sampling during the course of the study is approximately 100 mL. If additional pharmacokinetic and/or safety analysis is necessary, additional blood may be obtained. The total blood volume withdrawn from any single subject will not exceed 150 mL.

## 9.4 Time Tolerances and Windows

Visit windows for each visit are summarized in Section 9.1. Time tolerances and windows, as defined below, are permitted for this study.

- PK sample collection for MGS0008 (3 h postdose of investigation drug):  $\pm 5$  minutes
- Ketamine infusion at Day 6 (8 h postdose of investigation drug):  $\pm 2$  hours
  - Relative time to ketamine infusion for MRI scan, safety monitoring (continuous ECG, pulse oximeter, BP monitoring), PK sample collection (ketamine) and post-ketamine behavioral assessments must be maintained
- MRI scan (25 minutes predose of ketamine at Final Screening visit and 7 h 35 min postdose of investigational drug on Day 6) start time: - 30 minutes (up to - 55 minutes of initiation of ketamine infusion)
- Post ketamine MRI scan end time (15 min postdose of ketamine at Final Screening visit and 8 h 15 min postdose of investigational drug at Day 6): + 3 minutes (up to 18 minutes in duration)
- PK sample collection for ketamine (20 min postdose of ketamine at Final Screening visit and 8 h 20 min postdose of investigational drug at Day 6):  $\pm 5$  minutes
- Behavioral assessments at Day 6 (pre-ketamine; 6 h postdose of investigation drug): between assessments at 3h postdose and initiation of MRI scan
- Behavioral assessments at Final Screening Visit (pre-ketamine; - 2 h predose of ketamine): between "before behavioral assessments" and initiation of MRI scan
- C-SSRS at Day 6 (3 h postdose of investigational drug): between post administration of investigational product and initiation of behavioral assessments
- Pre-infusion assessments at Day 6 (Body weight, physical examination [including a neurological examination], vital signs and 12-lead ECG): between post administration of investigational product on Day 5 and initiation of Day 6 ketamine infusion

Any deviation found from the planned procedure time (outside the window noted above) must be documented and explained in the site source document by the site staff.

## 10 STATISTICAL METHODS

In addition to this section of the study protocol, a more detailed statistical analysis plan (SAP) will also be provided in a separate document. If circumstances arise during the study that make these analyses inappropriate or if improved methods become available, the SAP will take precedence and may be revised, as needed. Any revisions (both alternative and additional methods) to the SAP that are used in the final report, and reasons for such revisions, will be described in the final report.

### 10.1 Sample Size Determination

The evaluable sample size was selected based on sample sizes of available similar ketamine studies.

### 10.2 Analysis Populations

The PD analysis population will include all randomized subjects who received correct dosing and those with at least 1 baseline and with sufficient post-baseline PD data. Missing data will not be imputed and are to be excluded from the analysis.

The safety analysis population will include all subjects with at least one dose of study medication.

The PK analysis population will include all dosed subjects with evaluable MGS0008 PK data and may exclude subjects if their data are considered invalid due to relevant missing values, or if any other problem occurred during sampling, laboratory analysis, dosing or AEs which invalidates the concentration measurements.

### 10.3 General Analysis Conventions

The scope of most analyses will be primarily descriptive. For continuous measures, data will be summarized by means, standard deviations, medians, minimum, and maximum. Where appropriate, change from baseline will also be summarized. For categorical measures, data will be summarized with frequency counts and percentages. All data analyzed will be displayed in detailed listings.

### 10.4 Demographic and Baseline Characteristics

Demographics and baseline characteristics including but not limited to age, gender, body weight, height, BMI, BOLD fMRI data, BPRS and CADSS scores will be tabulated by group using descriptive statistics.

## **10.5 Pharmacodynamics (PD) Analysis**

### **10.5.1 Primary Endpoint**

To evaluate the treatment effect of TS-134 on ketamine-induced BOLD signals in pre-specified ROIs (ACC and anterior insula) in resting fMRI, analysis of covariance (ANCOVA) with change from baseline at Day 6 BOLD as the outcome predicted by baseline (Final Screening Visit) BOLD and treatment in 3-treatment groups (TS-134 20 mg group, TS-134 60 mg group and placebo group) will be performed, and the mean and 95% confidence interval (CI) will be estimated. Separate ANCOVAs will be fit to each ROI. Tests of treatment effect will be made within each treatment group, between each active treatment group (TS-134 20 mg group and TS-134 60 mg group) versus placebo group, and also between the two active treatment groups from the ANCOVA. A statistically significant negative change of BOLD found in the active treatment groups compared to placebo group would be consistent with the hypothesis. Cohen's d effect sizes will be reported using the standard deviation of baseline BOLD.

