## 6 STUDY DESIGN AND EVALUATION

### 6.1 Study Design

This study employs a randomized, single-blind, parallel-group design in healthy volunteers.

This study will enroll approximately 60 subjects. Following an up to 27-day outpatient Screening Period, eligible subjects will undergo an 8-day inpatient Treatment Period. Subjects will be randomized to one of three treatment groups in a ratio of 5:5:2 (25 subjects for a TS-134 20 mg group, 25 subjects for a TS-134 60 mg group and 10 subjects for a placebo group) (Figure 6-1). During the study, each subject will undergo a total of two ketamine sessions; a first session during a Screening Period and a second session on Day 6 of a Treatment Period. Each ketamine session will include one ketamine infusion with resting fMRI scanning from pre to post ketamine infusions. First and second ketamine sessions will be conducted at least 7 days apart. All randomized subjects will be dosed with TS-134 or placebo daily in a fed state, for 6 days during the study. TS-134 dose levels will be titrated according to the titration schedule shown in Table 6-1. Subjects' general health and safety status will be confirmed by a phone call one week following discharge from a Treatment Period.

[figure not shown]

Figure 6-1 Study Design

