## **6.2 Study Endpoints**

### **6.2.1 Primary Endpoint**

Changes in ketamine-induced BOLD fMRI signals in pre-specified ROIs (anterior cingulate cortex (ACC) and anterior insula) following administrations of TS-134

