8. History of recreational ketamine use, recreational PCP use, or an adverse reaction to ketamine. Subjects who have participated in prior research ketamine studies will be eligible providing they have participated in no more than 5 previous research ketamine infusions. Subjects can have infusions not more frequently than biweekly, and not more than 1/month on average, therefore subjects will need to wait 1 month if they had a single infusion and 6 weeks if they have had 2 closely spaced infusions prior to screening into the study.
9. Any subject who is unable to refrain from smoking throughout the study or with positive urine cotinine screen (> 400 ng/mL) at the Initial Screening Visit.
10. Any subject with a history and/or current evidence of serologic positive results for hepatitis B surface antigen, hepatitis C antibodies, or HIV antibodies 1 and 2 at the Initial Screening Visit.
11. History of violence, including any history of using a gun, knife, or other weapon with intent to harm someone, as well as a more than one physical fight without a weapon after the age of 18 years old (not including fights that happen during sports competition).

12. Presence or positive history of significant medical illness, including high blood pressure (SBP > 140 mmHg, DBP > 90 mmHg), low blood pressure (SBP < 100 mmHg, DBP < 60 mmHg), orthostatic hypotension (change in mean arterial pressure [ $1/3$  systolic +  $2/3$  diastolic] of > 20%) at Screening Visits (except for Final Screening Visit: Discharge) or Day -1 (Admission).
13. Any subjects who show subthreshold ketamine BOLD response (defined as % BOLD signal change of 0.5% at peak ketamine response) in ACC at Final Screening Visit.
14. Metal implants, pacemaker, other metal (e.g. shrapnel or surgical prostheses) or paramagnetic objects contained within the body which may present a risk to the subject or interfere with the MR scan, as determined in consultation with a neuroradiologist and according to the guidelines set forth in the following reference book commonly used by neuroradiologists: *Guide to MR procedures and metallic objects, F. G. Shellock, Lippincott Williams and Wilkins Philadelphia 2001*.
15. Claustrophobia.
16. Donation of one or more units of blood, plasma, or acute loss of an equivalent amount of blood within 60 days prior to Initial Screening Visit. (One unit= 450mL)

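### Section 10.5.1 tests within-group change as a treatment effect, but entry is selected on the ACC baseline, so regression to the mean can produce a false significant fall

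*Protocol*

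**What the plan says.** Three statements in the protocol bear on this point.

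- **Selection.** Section 7.2, exclusion 13, removes subjects with "subthreshold ketamine BOLD response (defined as % BOLD signal change of 0.5% at peak ketamine response) in ACC at Final Screening Visit". I read this as a response below 0.5%.
- **Baseline and outcome.** Section 10.5.1 specifies "analysis of covariance (ANCOVA) with change from baseline at Day 6 BOLD as the outcome". It describes this outcome as "predicted by baseline (Final Screening Visit) BOLD and treatment in 3-treatment groups". The baseline session is therefore the selection session.
- **Tests.** The same section continues: "Tests of treatment effect will be made within each treatment group, between each active treatment group" and placebo, and between the two active groups. The within-group tests cover all three arms, placebo included.

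Section 10.5.1 then ties the hypothesis to a between-group result: "A statistically significant negative change of BOLD found in the active treatment groups compared to placebo group would be consistent with the hypothesis". The primary endpoint (section 6.2.1) covers two regions, "pre-specified ROIs (anterior cingulate cortex (ACC) and anterior insula"), each with its own ANCOVA. Exclusion 13 concerns ACC only. Group sizes are "25 subjects for a TS-134 20 mg group, 25 subjects for a TS-134 60 mg group and 10 subjects for a placebo group" (section 6.1).

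**The concern.** A within-group change from baseline is not a treatment effect. Here it contains at least three things besides the drug.

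1. **Regression to the mean.** Subjects with low ACC readings at the first session are removed and those with high readings stay. Part of a high reading is measurement noise that will not recur on Day 6, so the expected change is negative in all arms.
2. **Session order.** Baseline is the first study ketamine session and Day 6 is the second.
3. **Setting.** Baseline is an outpatient visit, and Day 6 falls within an inpatient stay.

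The regression component points in the direction of attenuation, which is what the trial hopes to see. The same bias is also more likely to reach significance in an arm of 25 than in an arm of 10. A report could then say that ACC signal fell significantly on active treatment and did not on placebo, and present this as evidence of effect when no drug effect exists.

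**Working it through.** **Inputs from the protocol:** ANCOVA of change on baseline and three groups; group sizes 25/25/10; baseline equal to the selection session. A 95% interval is planned but no alpha is stated, so I take a two-sided 5% test, which is 2.5% in the negative direction. There is no power, SD or reliability figure to reproduce.

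**Assumptions, not in the protocol:** share of candidates screened out, p = 10–40%; test-retest correlation of the ACC response, r = 0.4–0.8; bivariate normal responses with equal means and SDs at both sessions (no drug effect, no true change); analysed measure the same as the screened one. On the last, section 9.3.5.1.3 says that mean and peak response are highly correlated, so selection on the peak carries over to the mean.

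**Step 1: expected change.** With baseline truncated below the cut-off a (in SD units), the expected within-group change is

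−(1 − r) × φ(a) / (1 − Φ(a)) SD.

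For p = 20%, a = −0.84, φ(a) = 0.28 and 1 − Φ(a) = 0.80. With r = 0.6 the change is −0.4 × 0.28/0.80 = −0.14 SD.

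**Step 2: why the covariate does not help.** The adjusted within-group mean is evaluated at the average baseline of the selected subjects, which already lies above the unselected mean by φ(a)/(1 − Φ(a)). The shift is the same in every arm, so it cancels in between-group contrasts and remains in within-group means.

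**Step 3: chance of a false significant fall.** The residual SD is √(1 − 0.6²) = 0.8.

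- Active arm: standard error 0.8/√25 = 0.16; 0.14/0.16 = 0.875; P(Z < −1.96 + 0.875) ≈ 14%.
- Placebo arm: standard error 0.8/√10 = 0.253; 0.14/0.253 = 0.55; P(Z < −1.96 + 0.55) ≈ 8%.

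**Step 4: simulation of the planned ANCOVA** (2000 runs per row, no drug effect). Within-group columns show significant falls only (nominal 2.5%). The last column is two-sided (nominal 5%).

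| Screened out | r | Expected ACC change (SD) | False fall, 20 mg / 60 mg | False fall, placebo | Active vs placebo, 20 mg / 60 mg |
|---|---|---|---|---|---|
| none | 0.6 | 0 | 3.3% / 3.2% | 2.6% | 5.4% / 5.4% |
| 10% | 0.8 | −0.04 | 5.3% / 5.2% | 3.9% | 5.0% / 5.4% |
| 10% | 0.4 | −0.12 | 10.2% / 9.8% | 6.6% | 5.7% / 5.0% |
| 20% | 0.8 | −0.07 | 9.1% / 9.0% | 6.2% | 6.0% / 5.4% |
| 20% | 0.6 | −0.14 | 13.8% / 13.8% | 8.4% | 4.6% / 4.4% |
| 20% | 0.4 | −0.21 | 20.7% / 21.6% | 11.0% | 4.8% / 5.3% |
| 40% | 0.8 | −0.13 | 19.5% / 18.4% | 8.8% | 5.4% / 4.5% |
| 40% | 0.4 | −0.39 | 52.2% / 55.2% | 26.3% | 5.7% / 5.0% |

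In the row for 20% and r = 0.6, at least one active arm shows a false fall in 25.5% of trials. A plain paired t-test there gives 11.6%, 11.4% and 7.6% for the three arms, so the result does not depend on the ANCOVA adjustment. Without selection the ANCOVA within-group rate already lies slightly above 2.5%, because its standard error treats the average baseline as fixed. That small excess is not due to exclusion 13.

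**Step 5: anterior insula.** It is not screened on. Its expected change moves only as far as ACC selection carries over through the correlation between the two regions, which the protocol does not give. The table does not apply to it directly.

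**The case against.** The strongest reply is that the plan does not read a within-arm fall as efficacy. The sentence following the list of tests makes the comparison with placebo the criterion, and randomisation protects that comparison. A reader might infer from the within-group problem that the primary analysis is invalid. The documents do not support this: all between-group contrasts stay near 5% under every assumption examined.

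A reader might also infer that selection will produce significant attenuation, even on placebo. That is too strong. At 20% screened out and r = 0.6, about 86% of trials show no significant fall in a given active arm, and a significant fall on placebo is less likely still. If the 0.5% threshold removes few candidates, or the measure is highly reliable, the excess is small. Both quantities are unknown.

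Finally, section 10.3 calls most analyses primarily descriptive and section 15.1 calls the study exploratory. A within-arm estimate is useful, for instance to show drift between sessions on placebo, and an interval that excludes zero conveys much the same message as a test.

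All of this stands and limits the severity. It does not remove the defect: the protocol still lists within-group tests among its tests of treatment effect for the primary endpoint. The hypothesis sentence does not withdraw them, and on placebo the label has no meaning.

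**Conclusion.** The concern holds as a moderate one. The direction of the bias in the within-group ACC tests follows from the protocol's own design, provided the ACC measurement is imperfectly reliable and the threshold removes someone. Its size rests on the two assumed quantities: per active arm, a false significant fall in roughly 5% to 53% of trials across the range examined, and about 14% at the middle values, where placebo shows about 8%. The unequal arm sizes favour a misleading pattern of a significant fall on active treatment and none on placebo. No size can be put on the order and setting effects, but a within-group test cannot separate them from the drug either. For anterior insula the selection effect is indirect and unquantified. The active-versus-placebo criterion is unaffected.

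**What to change.** In section 10.5.1, remove the within-group comparisons from the tests of treatment effect. Suggested wording: *Treatment effects will be tested by the ANCOVA contrasts of each active group with placebo and of the 60 mg group with the 20 mg group. The adjusted mean change in each group will be reported with its 95% CI for description only; it includes regression to the mean arising from exclusion 13 (directly for ACC) and any effect of session order and setting.*

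The caveat matters as much as the deletion, since a reader can turn an interval into a test. The report should also give the number of subjects screened out under exclusion 13, so that the likely size of the artefact can be judged. The change amounts to a few lines of text. It needs no additional data or subjects, and the between-group analysis is unchanged.

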### **10.5.2 Secondary Endpoint**

To evaluate the treatment effect of TS-134 on ketamine-induced BOLD signals in whole brain in resting fMRI, ANCOVA similar to analysis for the primary endpoint will be performed.

To evaluate the treatment effect of TS-134 on clinical measures of BPRS and CADSS, ANCOVA similar to analysis for the primary endpoint will be performed.

### **10.5.3 Interim Data Transfer**

Interim data transfer for change in BOLD signals in pre-specified ROIs in resting fMRI will be conducted for every 12 first and second ketamine session sets of assessments (i.e. following completion of 12th, 24th, 36th, 48h, and 60th subjects). Each interim analysis result will be provided to the sponsor within 7 days following the completion of BOLD assessments of respective cut-off subjects.

## **10.6 Safety Analysis**

Safety will be assessed for each group based on reported AEs, vital signs measurements, 12-lead ECGs, C-SSRS and clinical laboratory assessment results.

### **10.6.1 Adverse Events**

Treatment emergent adverse events (TEAEs) will be listed by lower level terms and summarized by system organ class with preferred term based on the MedDRA reporting system. The number and percentage of subjects who experience one or more TEAEs will be tabulated. The tabulation will be further classified by severity and relationship to investigational product.

AEs reported from the time of initial informed consent through the initial administration of an investigational product will be listed in a separate listing from TEAEs.

